# Impact of collaborative pharmaceutical care on in-patients’ medication safety: study protocol for a stepped wedge cluster randomized trial (MEDREV study)

**DOI:** 10.1186/s13063-017-2412-7

**Published:** 2018-01-08

**Keywords:** Stepped wedge study, Medication reconciliation, Medication review, Pharmaceutical care, Hospital pharmacist, Drug-related problem, Drug safety

## Abstract

**Background:**

Clinical pharmaceutical care has long played an important role in the improvement of healthcare safety. Pharmaceutical care is a collaborative care approach, implicating all the actors of the medication circuit in order to prevent and correct drug-related problems that can lead to adverse drug events. The collaborative pharmaceutical care performed during patients’ hospitalization requires two mutually reinforcing activities: medication reconciliation and medication review. Until now, the impact of the association of these two activities has not been clearly studied.

**Methods:**

This is a multicentric stepped wedge randomized study involving six care units from six French University Hospitals (each unit corresponding to a cluster) over seven consecutive 14-day periods. Each hospital unit will start with a control period and switch to an experimental period after a randomized number of 14-day periods. Patients aged at least 65 years hospitalized in one of the participating care units and having given their consent to be called for a 30-day and 90-day follow-up can be enrolled. For each 14-day period, 15 patients will be recruited in each care unit to obtain a total of 630 patients enrolled in all centers. Patients with a hospital stay of more than 21 days will be excluded. During the control period, there will be no clinical pharmacist in the care unit, whereas during the experimental period a clinical pharmacist will perform medication reconciliation and review with the healthcare team. The primary outcome will assess the impact of collaborative pharmaceutical care on preventable medication error rate. The secondary outcomes will evaluate the clinical impact of the strategy, the acceptance rate of pharmaceutical interventions, the induced and avoided costs of the strategy (cost-consequence analysis), and the healthcare team’s satisfaction.

**Discussion:**

This study will assess the impact of collaborative pharmaceutical care associating medication reconciliation and review at patient admission to hospital in terms of preventable medication error rate and costs. This activity will prevent and correct medication errors arising earlier in the hospitalization.

**Trial registration:**

ClinicalTrials.gov, NCT02598115. Registered on 4 November 2015.

**Electronic supplementary material:**

The online version of this article (doi:10.1186/s13063-017-2412-7) contains supplementary material, which is available to authorized users.

## Background

Drug-related problems (DRP) are a major concern in terms of public health because they have a serious clinical and economic impact on healthcare systems. A French multicentric study [1] reported that adverse drug events (ADE) were the second most common complication during hospitalization and were responsible for around 130,000 hospitalizations and 10,000 deaths a year in France. Apretna et al. estimated that each ADE cost > €5000 on average [2], yet around half of the severe ADEs are considered to be preventable [1]. Medication errors that can lead to ADE mainly occur at transition points in the patient’s healthcare pathway, mostly due to defects in the transmission of information at the prescription and the administration steps [3]. Also, 47–67% of patients have at least one error or discrepancy between the medications prescribed in the community and in the hospital. These errors are responsible for severe ADEs in 18–59% of cases [3–6]. Elderly patients are frequently frail and are at particularly high risk of DRPs. Indeed, 32–46% of hospitalized elderly patients experience at least one ADE [7, 8], of which 28% were deemed to be preventable [9].

For years, pharmaceutical care has been a key strategy to improve healthcare safety. Pharmaceutical care is a collaborative care approach which implies all the actors of the medication circuit in order to prevent and correct DRPs that can lead to ADEs. The collaborative pharmaceutical care performed during patients’ hospitalization requires two complementary activities: medication reconciliation and medication review. First, medication reconciliation is a collaborative process requiring the acquisition of the best possible medication history (BPMH) and its comparison against the hospital medication order [5, 10]. Studies have shown that medication reconciliation had a potential clinical impact by decreasing the rate of hospitalized patients with at least one unintended medication discrepancy (UMD) [10, 11]. This activity could be optimized by a clinical pharmacist based in care units [12]. A few studies have demonstrated that medication reconciliation can reduce readmissions [10, 13], whereas 10–24% of UMDs would lead to severe harm or would be life-threatening [11, 14]. Second, medication review is a multidisciplinary analysis of medication order initiated by the clinical pharmacist [10, 15, 16] that consists of optimizing the medication treatment by improving medication adherence, compliance with the recommendations, and decreasing DRPs (e.g. detection of potential inappropriate medications in elderly [PIM], non-treated therapeutic indications, better matching between medication and therapeutic indication, etc.). Medication review is supported by international standardized tools such as STOPP and START criteria [17, 18], Beers Criteria [19], and the Medication Appropriateness Index [20]. Medication reviews have highlighted PIM representing 16–71% of medications prescribed at hospital admission [21–23]. Moreover, PIM can lead to preventable ADEs [24]. Studies have shown that 38–79% of the patients benefiting from a medication review initiated by a pharmacist had at least one medication change made by the physician in the order [22, 25, 26]. Some studies have shown an impact of medication review on readmission induced by DRPs [25, 27].

However, very few studies have explored the health economics impact of medication reconciliation and medication review in European health systems. Malet-Larrea et al. showed that medication review associated with a clinical pharmacist follow-up led to an estimated saving of €273 per patient-year [28]. Moreover, a structured pharmacist review of medication supported by computerized clinical decision support software demonstrated a decrease of €807 in mean healthcare costs [29]. To the best of our knowledge, the economic impact of the association of medication reconciliation and review in a collaborative pharmaceutical care process has never before been studied.

The primary outcome of our study will assess the impact of collaborative pharmaceutical care on preventable medication error rate. The secondary outcomes will evaluate the clinical impact of the strategy, the acceptance rate of pharmaceutical interventions, the induced and avoided costs of the strategy (cost-consequences analysis), and the healthcare team’s satisfaction.

## Methods/design

A scientific committee will oversee the methodology of the study and ensure that the research organization is relevant to ensure the quality of the collection. A meeting of the Scientific Committee of the MEDREV study will be organized when the project is accepted, before the start of the study, and when the results are exploited.

### Design

A multicentric stepped wedge cluster randomized trial is proposed because randomization of patients was not possible in this study due to the high risk of contamination bias. Indeed, once the clinical pharmacist arrives in the care unit, the collaborative pharmaceutical care will lead to change in medical practices for all the patients, including the control group. Stepped wedge randomized trial designs involve sequential roll-out of an intervention to participants over a number of time periods. By the end of the study, all participants will have received the intervention, although the order in which participants receive the intervention is determined at random. The clusters will be hospital units. Each hospital unit will start with a control period and switch to an interventional period. The study design will be composed of seven consecutive 14-day periods (Fig. 1). Every 14-day period, one further hospital unit will switch to the interventional period until all the units are in the interventional period in the final 14-day period. The randomization by the project methodologist will define the point that each hospital unit will switch from the control to the interventional periods (Table 1).

**Fig. 1 Fig1:**
[figure not shown]
MEDREV study design

**Table 1 Tab1:** Centers, units, participants in the control period, and switch period

Hospital	Unit	Participants in the control period	Intervention starting period
CHU Rouen	Diabetes, endocrinology and metabolic diseases	Pharmacy students	Period 2
CHU Toulouse	Cardiology	Pharmacy students	Period 3
CHU Nice	Geriatric internal medicine	Pharmacy technicians	Period 4
CHU Grenoble	Geriatric acute medicine	Pharmacy students	Period 5
CHU Strasbourg	Internal medicine	Pharmacy technicians	Period 6
CHU Nîmes	Medical emergency	Pharmacy technicians	Period 7

*CHU* University Hospital Center

A randomized cluster trial would be difficult to conduct because the cluster number would be high and half of them would not benefit from the intervention.

### Setting and population

Six French University Hospitals which benefit from a strong expertise in clinical pharmacy and are dispersed across the country have agreed to participate (Table 1). Each center selected a short-term care unit in a medical specialty which welcomes the elderly. Only units in which there was no clinical pharmacist were eligible. The medical heads of all the units selected agreed to participate in the study.

All healthcare participants volunteered to participate in the study. In each center, two pharmacy students or two pharmacy technicians will participate in the control period (Table 1); two senior clinical pharmacists will participate in the interventional period. In each hospital center, the same clinical pharmacists will detect medication errors in both periods. All the participants benefited from a specific centralized training in order to harmonize their practices in each period. This training was performed over three days, the week before the study started. After data collection, controls will be carried out to ensure that pharmaceutical interventions have not been misclassified.

Patients aged at least 65 years, hospitalized in one of the participating care units, and having given their agreement to be called for a 30-day and 90-day follow-up could be enrolled. In each 14-day period, 15 patients will be recruited in each care unit no more than 24 h or 48 h after admission, respectively, in the week or weekend/public holiday. Finally, a total of 630 patients will be enrolled in the study. We will exclude patients with a hospital stay > 21 days, as there is a risk of there being too many medication modifications during the hospital stay.

The study procedures and assessments are outlined in the Standard Protocol Items: Recommendation for Interventional Trials (SPIRIT) checklist (see Additional file 1) and SPIRIT Figure (Fig. 2).

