### Outcomes

The primary outcome will assess the rate of patients having at least one preventable medication error (e.g. omission, wrong dose, wrong route of administration, etc.) on admission medication order (AMO). The primary outcome will be evaluated by clinical pharmacists retrospectively in the control period and prospectively in the interventional period.

Among the secondary outcomes, the potential clinical impact of each error detected will be assessed by a hospital physician and two clinical pharmacists (different from the investigators) by using a decision algorithm [30] adapted from the NCC MERP’s Index [31] and employing the high alert risk medication list of the Institute of Safe Medication Practices [32] and the North Carolina Narrow Therapeutic Index [33]. All of the experts, who are seniors specialized in geriatrics, will blindly perform the analysis, i.e. without knowing the hospital center concerned, after completion of patient recruitment for all the centers. The potential clinical impact will also be evaluated by the rate of patients at high risk of ADEs according to Trivalle’s score [9, 34].

Other secondary outcomes will be: (1) the acceptance rate of pharmaceutical interventions during the interventional period; (2) the readmission and mortality rates 30 and 90 days after discharge; (3) the length of hospital stays; (4) the satisfaction of care providers involved in the collaborative pharmaceutical care (assessed by postal or electronic mail after the end of the 90-day follow-up); and (5) the induced and avoided costs of the strategy. For this last outcome, we will estimate the induced costs by measuring the time spent performing the collaborative pharmaceutical care. We will also assess the avoided costs by estimating the healthcare consumptions dues to medication errors by using the results of a French national study concerning ADE occurrence and cost [1] and/or by using an expert concertation via a DELPHI method.

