### Statistical analysis

Descriptive statistics will be reported as counts and percentages for categorical variables, means and standard deviations for continuous variables with normal distribution, and median and quartiles for others. Comparisons of baseline characteristics and of putative risk factors between the two periods will be performed. The primary outcome will assess the rate of patients having at least one preventable medication error through a mixed effect logistic regression model [40]. Let Y_ij_ be the *j*th observation (j = 1…m_i_) in the *i*th cluster (i = 1,2,…,K). The intervention variable is X_*i*_. The logistic mixed effect model is$$ \mathrm{Logit}\left({\mathrm{p}}_{\mathrm{i}\mathrm{j}}\right)={\upbeta}_0+{\upbeta \mathrm{X}}_{\mathrm{i}}+{\mathrm{Z}}_{\mathrm{i}} $$

Where Z_i_ is the random effect for cluster *i*, normally distributed with mean 0 and variance τ^2^, X_i_ is the group indicator. Therefore, the rate of patients having at least one preventable medication will be modeled as:$$ {\mathrm{p}}_{\mathrm{i}\mathrm{j}}=\mathrm{E}\left({\mathrm{Y}}_{\mathrm{i}\mathrm{j}}|{\mathrm{X}}_{\mathrm{i}},{\mathrm{Z}}_{\mathrm{i}}\right) $$

The other effects of putative predictors of the differences in medication adherence between patients from the control and the interventional periods will be evaluated. The secondary outcomes will be evaluated by descriptive and classical statistics: the acceptance rate of pharmaceutical interventions during the interventional period will be estimated (%) only in interventional period; the rate of readmission;, mortality at 30 and 90 days will be estimated and compared using a Chi-square test; the length of stay will be estimated and compared using a non-parametric test; and the descriptive statistics will be used to describe the results or the satisfaction of care providers.

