## Discussion

This trial will investigate the impact of the collaborative pharmaceutical care on preventing and correcting inpatients’ medication errors and costs.

The patient recruitment is a critical parameter to guarantee the study feasibility. The care units participating in the study have been chosen for having more than one eligible patient admission a day. Two-thirds of them are not specialized in the elderly whereas some of them are geriatric specialized units. All are medical units with a large number of beds (more than 15) and a mean length of stay of 2–5 days. In order to be maximally efficient, the intervention will need to start as soon as possible after patient admission. The patient interview during the medication reconciliation process will take around 15 min.

In order to standardize the collaborative pharmaceutical care, the scientific committee has created a specific training program for the students and technicians involved in the control period and for the senior clinical pharmacists involved in the interventional period. This program was elaborated by expert clinical pharmacists who are members of the French Society of Clinical Pharmacy. To ensure the performance of the intervention, they have written quality forms (i.e. checklist process and worksheets). To harmonize the data collection, phone interviews will be centrally performed by two officers.

The next step of this phase III study, if the results lead to effectiveness of the collaborative pharmaceutical care, is to assess the implementation and to determine whether others can reliably replicate the intervention and results in uncontrolled settings over the long term.

This study has the support of the French Society of Clinical Pharmacy which is expected to write recommendations and promote the implementation of the collaborative pharmaceutical care in all French health facilities in order to improve medication safety.

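### Removing enrolled patients whose stay later exceeds 21 days selects on a post-enrolment variable and truncates the length-of-stay outcome, although few patients are likely to be affected

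*Protocol article*

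**What the plan says.** Under Setting and population, the protocol article gives the recruitment window as "15 patients will be recruited in each care unit no more than 24 h or 48 h after admission, respectively, in the week or weekend/public" (the quote breaks off there; the longer limit covers weekends and public holidays). The same paragraph continues: "We will exclude patients with a hospital stay > 21 days", and gives the reason "as there is a risk of there being too many medication modifications during the hospital stay". The abstract repeats the rule ("Patients with a hospital stay of more than 21 days will be excluded"), and the legend of the SPIRIT figure limits the in-hospital interval to between 1 and 21 days.

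Under Outcomes, the primary outcome is the "rate of patients having at least one preventable medication error", judged on the admission medication order. The other secondary outcomes include readmission and mortality 30 and 90 days after discharge, "3) the length of hospital stays", and costs. Statistical analysis adds that "the length of stay will be estimated and compared using a non-parametric test". The Discussion describes all participating units as having "a mean length of stay of 2–5 days". Trial status reports 622 patients enrolled.

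**The concern.** Nobody can know at 24 or 48 h that a stay will pass 21 days. The rule therefore works after enrolment and, in interventional periods, after the pharmacist has started work. It also depends on a variable that the trial tests as an outcome. Three things follow.

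- **Length of stay is truncated.** No analysed patient can have a stay above 21 days, so any effect on the long tail is invisible.
- **Selection may differ by condition.** If the intervention shortens or lengthens stay, the share removed differs between control and interventional periods, and the retained groups are no longer the groups as enrolled. Readmission and mortality, counted from discharge, and costs are described without any other analysis set, so they inherit the same selection.
- **The reason does not reach the primary outcome.** Medication changes later in the stay cannot alter whether the order written at admission contained an error.

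**Working it through.** **Inputs from the article.** Cut-off 21 days; mean stay 2–5 days (Discussion); 6 units × 7 periods × 15 patients; difference 0.30, variance 0.20, intra-class correlation 0.05 (Sample size calculation).

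**Assumptions not in the article.** Lognormal stays with SD 1.0 or 1.6 times the mean; two-sided alpha 0.05; 630 counted before the exclusion, with no replacement.

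**1. The plan's own figures.** N = 6 × 7 × 15 = 630, as stated. The closed-form stepped wedge variance (Hussey and Hughes; fixed period effects, random cluster effect, between-cluster variance 0.20 × 0.05/0.95 = 0.0105) gives SE = 0.0599. Power = Φ(0.30/0.0599 − 1.96) = 99.9%, in line with the stated 99%.

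**2. Share removed.** For mean m and ratio c = SD/mean: s² = ln(1 + c²), μ = ln m − s²/2, a = (ln 21 − μ)/s, P = 1 − Φ(a).

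| Mean stay (days) | SD/mean | P(stay > 21) | Of 630 |
|---|---|---|---|
| 2 | 1.0 | 0.06% | 0.4 |
| 2 | 1.6 | 0.40% | 2.5 |
| 3.5 | 1.0 | 0.51% | 3.2 |
| 3.5 | 1.6 | 1.56% | 9.9 |
| 5 | 1.0 | 1.62% | 10.2 |
| 5 | 1.6 | 3.31% | 20.9 |

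**3. Effect on the length-of-stay summary at mean 5 days.** Truncated mean = (m − E[X; X > 21])/(1 − P), with E[X; X > 21] = m Φ(s − a).

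- SD 5: (5 − 0.478)/0.984 = 4.60 days.
- SD 8: (5 − 1.194)/0.967 = 3.94 days.

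Truncated median = exp(μ + s Φ⁻¹(0.5(1 − P))).

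- SD 5: 3.54 to 3.48 days, a fall of 0.06.
- SD 8: 2.65 to 2.53 days, a fall of 0.12.

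**4. If the intervention did shorten stay.** Take an illustrative true reduction in mean stay from 5 to 4 days, same log-SD in both conditions.

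| Log-SD | Removed, control | Removed, intervention | Difference in means among those kept (true 1.0 day) |
|---|---|---|---|
| 0.8 | 1.4% | 0.7% | 0.82 |
| 1.0 | 2.6% | 1.5% | 0.68 |
| 1.2 | 3.6% | 2.4% | 0.55 |

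The mean difference would be understated by 18–45%. The planned test is rank-based and depends less on the tail, so these figures are an upper guide for it.

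**5. Primary outcome and power.** Assume error rates of 46% and 16% (difference 0.30) and the largest pair above, 3.6% and 2.4% removed.

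- Every removed patient had an error: (0.46 − 0.036)/0.964 − (0.16 − 0.024)/0.976 = 0.440 − 0.139 = 0.300.
- All removed controls and no removed intervention patients had an error: 0.440 − 0.16/0.976 = 0.276.
- The reverse arrangement: 0.46/0.964 − 0.139 = 0.338.

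Even these last two extremes move the difference by less than 0.04. Scaling the cell size for a 10% loss still leaves power at 99.8%.

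**The case against.** The strongest reply is that the rule is harmless here. It is the same in both periods, and the units are short-stay. If the intervention leaves length of stay unchanged, the exclusion need not differ between conditions and mainly narrows the target population. The planned comparison is rank-based, and the median moves by about 0.1 day at most. The reason given also has some force for the secondary outcomes: after a long stay with many order changes, a readmission is harder to tie to an intervention on the admission order. All of this stands, and it limits the size of the problem. It does not make the rule sound, because the trial tests for an effect on length of stay and cannot presume there is none. Difficulty of attribution after long stays is a case for a sensitivity analysis.

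A reader might infer more than the article supports.

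- One could take the primary result to be materially biased. Step 5 shows that it would move little.
- One could put the loss at 6–10%. That needs mean stays of 8–10 days, and the article gives 2–5 days for all units.
- One could argue that long-stay patients die or return more often, or have most to gain. The article says neither.

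**Conclusion.** The point holds as a flaw of design in the analysis population. The rule selects on a post-enrolment variable that is itself an outcome, it truncates length of stay at 21 days, and its stated reason does not apply to the primary outcome. The readmission, mortality and cost results would rest on the same selected patients.

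The size is modest: about 0.1–3.3% of patients lost, and little likely effect on the primary outcome, power or the planned rank test. Mean stay, which is more sensitive to the tail, is the summary most exposed. These figures depend on the assumed lognormal shape and spread; only the mean of 2–5 days comes from the article. Differential exclusion is conditional on the intervention changing stay, which is a hypothesis of the trial and not an established fact.

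**What to change.** Define the main analysis set as all enrolled patients for the primary outcome and for length of stay, and for readmission, mortality and costs wherever the data were or can be collected. Keep the restriction to stays of 21 days or less as a sensitivity analysis only. Report the number of patients over 21 days by period and cluster, so that any imbalance is visible.

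The cost is a change of wording plus keeping a small number of long-stay patients in the database and following them up. No extra recruitment is needed. With 622 patients already enrolled, some follow-up calls for long-stay patients may not have been made. In that case, state which outcomes are missing for them and for how many.
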